### Data management {19}

Paper Case Report Forms (CRF) and patient notes will be stored at research sites. Electronic CRFs will be stored in Red Pill/Sealed Envelope, a GCP compliant database used by UCL’s Priment Clinical Trials Unit. Data entry will only be carried out following training on the secure, password-protected database. Trial data will be coded at the entry stage using predefined structures. Back-ups will be made of the trial database on a monthly basis.

Checks of data entry and eligibility are carried out at baseline for all participants prior to randomisation. Data will also be validated with source data verification (first 5 participants at each site, and 10% of all participants), database checks and statistician’s checks. Queries and missing data will be monitored, with the aim of resolution within a month. At sites with a high level of discrepancy, staff will be retrained. Delivery of the intervention will be monitored for adherence to protocol and correct timing of intervention using session log records.

Once all data have been received and cleaned, the database will be locked for analysis, without the possibility of further edits. At the end of the trial, all essential documentation will be archived securely for a minimum of 10 years. In addition to this data management summary, the trial team has also developed detailed guidance for sites (plans on Data Management, Monitoring, Source Data Verification, and a database guidance document) which are stored in the Trial Master File and Investigator Site Files.

### Confidentiality {27}

Referral forms for named, potential participants who have agreed to be referred to the study and Identifiable information about trial participants will all be stored in the University College London Data Safe Haven, a highly secure data store with access limited to essential study researchers. A key linking participant names and ID numbers will also be stored in the Data Safe Haven.

All data collected about participants, including personal data such as demographic characteristics, will be stored in the trial electronic “Sealed Envelope” database where participants are identified only by their trial ID number. Paper copies of data collection forms will similarly be identified only by participant ID and will be stored securely in university premises.

### Plans for collection, laboratory evaluation and storage of biological specimens for genetic or molecular analysis in this trial/future use {33}

This trial does not involve collection or storage of biological specimens.

## Statistical methods

### Statistical methods for primary and secondary outcomes {20a}

A Statistical Analysis Plan will be finalised and approved prior to commencing analysis. The analyses and subsequent reporting will be guided by the CONSORT recommendations [40]. Analyses will be performed on a modified intention to treat basis, in which participants will be analysed according to their allocated group using all available data for a given outcome and time-point. A CONSORT diagram will be presented to provide a detailed description of participant numbers at each time-point during the trial.

The baseline demographic and clinical characteristics of the participants will be presented in a table summarised separately by study arm. Categorical variables will be reported as counts and percentages. Continuous variables will be summarised as either means and standard deviations (SD) or medians and interquartile ranges, depending on the distribution of the data. No statistical tests will be performed to assess baseline differences between study arms. Any notable imbalances may lead to additional adjusted sensitivity analyses.

#### Primary outcome statistical analysis

The primary analysis of the PHQ-9 score at 8 months follow-up (end-of-treatment) comparing intervention and control groups will use a mixed model (estimated using REML, with the Kenward-Roger adjustment) to perform an individual-level analysis and will follow guidance [41] in adjusting for navigator clustering in the intervention arm only (random coefficient model): specifically, each control subject will be treated as a cluster of size 1. This model will also adjust for baseline PHQ-9 score and site using fixed effects. The estimated intervention effect will be reported with a 95% confidence interval and *p*-value. This analysis will use available data only. All modelling assumptions will be checked. In particular, a confirmatory analysis will be performed using the heteroscedastic model [41] which allows the residual variance for intervention and control groups to differ. Withdrawals from the study, loss to follow-up and other missing outcome data will be summarised separately by randomised group. The primary analysis will be a complete case analysis. However, we will investigate whether there are any predictors of missingness. If any are found, these will be included in an adjusted analysis as a supportive analysis.

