#### Secondary outcomes

We will also report PHQ-9 total score data at 4-, 11- and 14-month follow-up points.We will create two further variables from PHQ-9 scores for analysis at 8 and 14 months follow-up points: (a) recovery from depression, where PHQ-9 score will be dichotomised for analysis, where ≥ 10 is the clinical cut off for depression [20]; and (b) Substantial improvement in depression: a dichotomous variable for whether or not a reduction in PHQ-9 score since baseline of at least 5 points has been achieved, based on the established threshold for reliable and clinically significant change [29].The UCLA Loneliness scale (ULS-8) [30] is an 8-item scale measuring loneliness which has good established psychometric properties and has been used previously in mental health populations (all assessment points).The Generalised Anxiety Disorders Scale (GAD-7) [31] is a seven-item self-report measure of anxiety (baseline, 8 months follow-up, 14 months follow-up).The Questionnaire on the Process of Recovery (QPR) [32] is a 15-item self-report measure of personal recovery (baseline, 8 months follow-up, 14 months follow-up).The Multiple Identities Scale (MIS) [33] is a four-item self-report scale measuring multiple social identities (baseline, 8 months follow-up, 14 months follow-up).The Brief Rosenberg self-esteem scale (B-RSES) [34] is a 5-item scale measuring self-esteem (baseline, 8 months follow-up, 14 months follow-up).The Discrimination and Stigma Scale (DISC-12 subscale) [35] is an interview-based scale which measures experiences of mental health-related discrimination in key areas of everyday life and social participation, including work, marriage, parenting, housing, leisure and religious activities. To measure self-stigma, we will be using the four-item self-stopping behaviours subscale from the Discrimination and Stigma Scale (baseline, 8 months follow-up, 14 months follow-up).Lubben Social Network Schedule (LSNS-6) [36] is one of the most widely used questionnaires to quantitatively assess social network size and we will use the six-item Lubben Social Network Schedule to measure social network size (baseline, 8 months follow-up, 14 months follow-up).The EQ-5D-5L [24] is a five-item self-report health outcome measure (baseline, 8 months follow-up, 14 months follow-up).The Recovering quality of life (ReQoL) [25] is a 10-item self-report measure of quality of life developed for use across all mental health populations (baseline, 8 months follow-up, 14 months follow-up).Client Service receipt Inventory (CSRI) [26] is a tool used to collect information on the range of services and supports participants may use (baseline, 8 months follow-up, 14 months follow-up).Daytime Activities Questionnaire (all assessment points).The Credibility and Expectancy questionnaire [37] is a six-item scale that measures treatment expectancy and credibility. We will use a single-item adapted version (Baseline).

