### Sample size {14}

We will recruit 306 participants. The standard calculation to detect a 0.4 standard deviation (sd) difference in PHQ-9 depression score between arms with 90% power and 5% alpha requires 132 participants per arm. Adjusting for baseline PHQ reduces the sample size by *r*-squared, where *r* is the correlation between baseline and follow-up outcome values [38]. Assuming a correlation of 0.5 and 15% attrition (informed by the feasibility trial [7]) results in a sample size of 117 participants per arm. Assuming four sites, three navigators per site, and an ICC for clustering by navigator of 0.05, results in a design effect of 1.6 (based on 13 participants per navigator). Inflating the sample size for clustering in the intervention arm only (to 188), then adjusting group sizes to be equal, produces a sample size of 153 participants per arm.

In response to peer review comments, we have checked the sample size calculation using simulation and have found that we do obtain 90% power, as calculated, when analysing the data using a mixed model with ML, treating each control subject as a cluster of size 1. However, as noted by the reviewer, the confidence interval coverage and type I error are slightly improved by analysing the data using REML with the Kenward-Rogers adjustment. This results in a slight loss of power but is the analysis we now intend to use. The power to detect a (standardised) difference of 0.4 is reduced to 87%, or equivalently, we have 90% power to detect a difference of 0.42. This still provides 90% power to detect a minimum personally meaningful difference on PHQ-9 between groups of about 2 points [39].

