### Methods for additional analyses (e.g., subgroup analyses) {20b}

Several additional analyses are planned. These include (1) an analysis to adjust for any baseline imbalance caused either by chance or missing data; (2) an analysis that includes PHQ-9 data from all five time-points (including baseline) using a 3-level mixed model; (3) an analysis to explore the mediating effect of loneliness on depression across the five time-points (main results permitting); (4) an analysis to explore the effect of baseline expectations and credibility of the intervention on the outcome (main results permitting). There are no planned subgroup analyses.

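### The additional adjusted analysis is chosen by observed baseline imbalance; name its covariates in advance by prognosis instead (minor)

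*Protocol article*

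**What the plan says.** The primary outcome section specifies a mixed model for 8-month PHQ-9 (REML, Kenward-Roger), with navigator clustering in the intervention arm only. On covariates it says: "This model will also adjust for baseline PHQ-9 score and site using fixed effects". Site is also the only stratification factor named under Sequence generation.

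Further adjustment appears in three places, always in a secondary role:

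- **Statistical methods {20a}**, after ruling out significance tests of baseline differences: "Any notable imbalances may lead to additional adjusted sensitivity analyses".
- **Additional analyses {20b}**, first item in the list: "an analysis to adjust for any baseline imbalance caused either by chance or missing data".
- **Primary outcome analysis and {20c}**: predictors of missingness, if found, go into a supportive or sensitivity analysis.

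Other baseline scores are available. Under Secondary outcomes, GAD-7 "is a seven-item self-report measure of anxiety (baseline, 8 months follow-up, 14 months follow-up"), and ULS-8 is collected at every assessment point. The Background describes loneliness as independently predictive of recovery from depression, without giving a strength.

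Under Sample size, after the move to REML with Kenward-Roger, "The power to detect a (standardised) difference of 0.4 is reduced to 87" per cent.

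**The concern.** The plan rightly declines to test baseline differences, but then lets observed imbalance decide what the additional analysis adjusts for. Whether adjustment helps depends mainly on how strongly a covariate predicts the outcome. A covariate unrelated to 8-month PHQ-9 can be badly imbalanced and leave the treatment estimate essentially unchanged. A prognostic covariate that happens to be balanced would still reduce residual variance, yet an imbalance rule passes it over.

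The rule is also loose. *Notable* has no threshold in {20a}, *may* makes the analysis optional there, and {20b} lists it as planned. Under Procedure for unblinding, baseline scores can be downloaded by group (labelled 1 and 2) to check balance. The covariate set could therefore be settled after baseline data by group have been seen.

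Two things are at stake: how interpretable the adjusted analysis is, and a modest amount of precision. Both matter a little more because the intended analysis has already cost 3 points of power (90% to 87%).

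**Working it through.** **1. Reproduce the plan's figures (Sample size {14}).** The starting point is "The standard calculation to detect a 0.4 standard deviation (sd) difference in PHQ-9 depression score between arms", which "with 90% power and 5% alpha requires 132 participants per arm".

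- Unadjusted n per arm, two-sided 5%: 2 × (1.960 + 1.282)² / 0.4² = 131.3, so 132.
- Baseline adjustment ("Adjusting for baseline PHQ reduces the sample size by" r-squared), r = 0.5: 132 × (1 − 0.25) = 99.
- 15% attrition: 99 / 0.85 = 116.5, so 117.
- Design effect: 1 + (13 − 1) × 0.05 = 1.6; 117 × 1.6 = 187.2, so 188.
- Equal arms: (188 + 117) / 2 = 152.5, so 153.
- Power check: 153 × 0.85 = 130.05 analysed per arm; SE = √(0.75 × (1.6 + 1) / 130.05) = 0.1225; power at 0.4 by normal approximation 90.4% (stated 90%).
- Using a t distribution on about 30 degrees of freedom as a stand-in for Kenward-Roger: 88.5% (stated 87%).

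The chain reproduces. Baseline PHQ-9 is already credited with 25% of the variance.

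**2. What further covariates could add.** Start from the stated 87% at 0.4 SD. The implied SE is 0.4 / (1.960 + 1.126) = 0.4 / 3.086 = 0.1296. If further covariates explain a fraction p of the variance left after baseline PHQ-9, the SE is multiplied by √(1 − p), and power = Φ(3.086 / √(1 − p) − 1.960). The article gives no p, so this range is assumed:

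| p (partial R²) | Total R² = 0.25 + 0.75p | SE reduction | Power at 0.4 SD |
|---|---|---|---|
| 0 | 0.25 | – | 87% |
| 0.02 | 0.265 | 1.0% | 87.7% |
| 0.05 | 0.2875 | 2.5% | 88.6% |
| 0.10 | 0.325 | 5.1% | 90.2% |

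To return to 90%: p = 1 − (3.086 / 3.242)² = 0.093.

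This scales the whole variance. If participant-level covariates leave the between-navigator part untouched, the gain is smaller. Taking that part as 0.75 × 0.05 / 12 = 0.0031 of the squared SE 0.0168, the remaining 0.0137 is scaled by (1 − p). Power is then 87.5%, 88.3% and 89.6% for p = 0.02, 0.05 and 0.10.

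**3. How readily chance produces an imbalance.** With 153 per arm, a standardised baseline difference has SE √(2/153) = 0.114. Taking 0.2 SD as an illustrative reading of *notable* (the article sets no threshold), 0.2 / 0.114 = 1.75, a two-sided probability of 0.080 per covariate. For independent covariates, the chance that at least one exceeds it is 1 − 0.920^k: about 34% for k = 5, 57% for k = 10 and 71% for k = 15.

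**4. Effect on type I error.** In a simulation (20,000 runs, 130 per arm, five covariates with joint R² 0.09, no clustering, Monte Carlo SE about 0.15 points), rejection under the null was 5.3% unadjusted, 4.8% when adjusting only for covariates beyond 0.2 SD, and 5.7% if the smaller of the two p-values were taken. Adjusting on imbalance does not itself inflate the error rate; choosing between results does so slightly.

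**The case against.** A reader might infer that the primary result depends on covariates picked after looking at the data. The article does not support that. The primary model is fixed, contains the baseline value of the outcome and the only named stratifier, and has no imbalance trigger. The imbalance rule reaches only sensitivity and additional analyses. The analysing statistician sees the groups as 1 and 2, and taking the smaller p-value is not open to the team because the primary analysis is named.

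A reader might also infer that leaving out GAD-7 and ULS-8 is an error that costs the trial its 90% power. That does not stand either. Two covariates are a defensible choice and match the sample size calculation. The 87% is disclosed, and the article states 90% power at 0.42 SD. No strength is given for either score, and the entry threshold on the DJG-6 loneliness scale may narrow the spread of baseline loneliness. Nor is imbalance the only route to further adjustment, since predictors of missingness are another.

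The remaining objection is that covariates for a sensitivity analysis, and the meaning of *notable*, belong in the statistical analysis plan, which is not shown and may already name them. That is fair for the missing detail. It does not cover the criterion, which the article itself states in two sections and which is a poor one.

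**Conclusion.** The concern holds for the additional adjusted analysis only, and it is minor. Observed baseline imbalance is the stated basis for further adjustment, and it is inferior to choosing covariates in advance for their expected relation to outcome. The primary estimate, interval and p-value are unaffected, and no material inflation of type I error was found.

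The precision argument is secondary and conditional. At an assumed partial R-squared of 0.02 to 0.05, power at 0.4 SD moves from 87% to about 88% to 89%. About 0.09 to 0.10 would be needed to return to 90%, or somewhat more if the navigator variance is not reduced. The article has no figure that places ULS-8 and GAD-7 anywhere in that range; the Background statement about loneliness gives a direction, not a size.

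**What to change.** Before any outcome is seen by arm, name baseline ULS-8 and baseline GAD-7 as fixed effects in one of two places:

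- in the primary model, alongside baseline PHQ-9 and site; or
- if the primary model is kept as it is, in a single pre-specified supportive adjusted analysis, labelled as such.

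Use this in place of the imbalance-triggered adjustment in {20a} and the first item in {20b}, so that the two sections agree. Add a simple rule for any missing baseline score, such as filling with the overall mean across both arms, so that no participant is dropped. The planned analysis using predictors of missingness can stay.

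The cost is a few sentences and two degrees of freedom. No new data are needed. If the covariates go into the primary model, the change should be recorded as a protocol amendment; if they go into the supportive analysis, wording in the statistical analysis plan and matching text in the protocol are enough.

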#### Secondary outcome statistical analysis

The effect of the intervention on secondary outcomes will be assessed using analogous methods to those used for the primary outcome. Most of the secondary outcomes are numerical and hence will be analysed using a similar model to that used for the primary outcome, whereas the binary outcomes (those derived from PHQ-9) will be analysed using a mixed-effects logistic regression model. *P*-values will not be reported for secondary analyses. The number and type of adverse events will be summarised by study arm.

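### If the binary PHQ-9 outcomes keep a navigator random effect in the intervention arm only, the logistic model's odds ratio is slightly off 1 when the arms have equal event rates

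*Protocol article*

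**What the plan says.** Under Primary outcome statistical analysis, the 8-month PHQ-9 score is analysed with a mixed model "adjusting for navigator clustering in the intervention arm only (random coefficient model"). Each control participant is coded as a cluster of size 1, and baseline PHQ-9 and site enter as fixed effects.

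Under Secondary outcome statistical analysis, intervention effects "will be assessed using analogous methods to those used for the primary outcome". For the two dichotomies of the PHQ-9 the text continues: "whereas the binary outcomes (those derived from PHQ-9) will be analysed using a mixed-effects logistic regression model". These dichotomies are recovery (cut-off 10) and a fall of at least 5 points from baseline, each at 8 and 14 months. No p-values are to be given for secondary analyses. The article does not repeat the random-effect structure for the logistic model and does not name the effect measure to be reported.

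The Objectives section frames the questions as a comparison of people randomised to be offered the programme with controls.

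**The concern.** With an identity link, a mean-zero navigator effect in one arm leaves the difference in means unchanged, so the random coefficient model suits the PHQ-9 score and the other numerical outcomes. With a logit link this no longer holds. Averaging over navigators pulls the intervention arm's risk towards 50%. The model therefore places the average-navigator log-odds further from zero than the arm's overall risk implies. The control side has no navigator term and undergoes no such shift.

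The default treatment coefficient then answers a different question from the one in the objectives. Two arms with the same recovery rate would show an odds ratio a little away from 1. Because no p-values accompany these outcomes, the point estimate and its interval carry the whole message, so the meaning of the estimate should be fixed.

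**Working it through.** **1. The plan's own figure.** Inputs from Sample size {14}: "The standard calculation to detect a 0.4 standard deviation (sd) difference in PHQ-9 depression score between arms with 90% power and 5% alpha"; "Assuming a correlation of 0.5 and 15% attrition"; "Assuming four sites, three navigators per site, and an ICC for clustering by navigator of 0.05".
- Unadjusted: 132 per arm.
- Baseline adjustment: 132 × (1 − 0.5²) = 99.
- Attrition: 99 / 0.85 = 116.5, so 117.
- Design effect: 1 + (13 − 1) × 0.05 = 1.6.
- Intervention arm: 117 × 1.6 = 187.2, so 188.
- Equal groups: (117 + 188) / 2 = 152.5, so 153.

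Every step matches the article. It also supplies the design for the check: 4 × 3 = 12 navigators, and 153 × 0.85 ≈ 130 analysed per arm.

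**2. The model.** For participant i with navigator j:

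logit P = a + b·trt + u_j·trt, with u_j ~ N(0, s²).

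The control risk is expit(a). The intervention risk is E[expit(a + b + u)]. For a common risk p, a = logit(p), and b is solved by Gauss-Hermite quadrature so that the intervention risk also equals p. The odds ratio under equal rates is exp(b).

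**3. Navigator variance.** The article gives an ICC only for the continuous PHQ-9. Placed on the latent logit scale (an assumption), s² = ICC/(1 − ICC) × π²/3:
- ICC 0.05: 0.05/0.95 × 3.290 = 0.173.
- ICC 0.10 (assumed, not in the article): 0.10/0.90 × 3.290 = 0.366.

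**4. Odds ratio when both arms have the same event rate.** The rates are assumptions, since the article gives none for this trial.

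| Event rate | ICC 0.05, latent | ICC 0.10, latent | ICC 0.05, proportion scale |
|---|---|---|---|
| 10% | 0.934 | 0.868 | 0.815 |
| 20% | 0.951 | 0.901 | 0.910 |
| 30% | 0.967 | 0.934 | 0.952 |
| 40% | 0.984 | 0.967 | 0.978 |
| 50% | 1.000 | 1.000 | 1.000 |
| 60% | 1.017 | 1.034 | not computed |

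For example, at 20% and latent ICC 0.05, b = −0.0506 and exp(−0.0506) = 0.951. Conversely, a model odds ratio of exactly 1 with 20% control recovery corresponds to 20.8% in the intervention arm.

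**5. With a prognostic covariate.** The planned model would adjust for baseline PHQ-9. As an illustration, take a normal covariate with latent correlation 0.5, that is a logit-scale SD of √(0.25/0.75 × 3.290) = 1.05, in both arms. The latent-ICC-0.05 values then move to about 0.96 at 20% and 0.98 at 30%, slightly nearer 1.

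**6. Finite-sample check.** This used 1,500 simulated trials per setting, with equal true rates, 12 navigators, 130 analysed per arm and no covariates.

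| ICC, rate | Mean model log OR | Mean crude log OR | Gap | Theory | SD of estimate |
|---|---|---|---|---|---|
| 0.05, 20% | −0.065 | −0.011 | −0.054 | −0.051 | 0.367 |
| 0.05, 30% | −0.028 | 0.007 | −0.034 | −0.034 | 0.302 |
| 0.10, 20% | −0.113 | −0.015 | −0.098 | −0.104 | 0.387 |

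The shift persists in fitted models. Against sampling error it is 0.051 / 0.367 = 0.14 SD at 20% and 0.034 / 0.302 = 0.11 SD at 30%.

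**The case against.** The strongest reply is that the article does not fix the model criticised here. The intervention-arm-only structure is written for the PHQ-9 score and reaches the binary outcomes only through the reference to analogous methods. No odds ratio is promised, and a statistical analysis plan that is not shown may specify a standardised summary. If the singleton controls were given a random intercept with the same variance, both sides would be conditional in the same way and equal rates would give exactly 1. This stands as far as it makes the point conditional. It does not remove it, because shared variance is not the random coefficient model that the primary section describes, and an odds ratio is the default output of the logistic model named.

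A reader might infer that the coefficient is biased or has no meaning. The documents do not support that. It is a defined contrast, an average navigator against none, and differing from another estimand is not bias. Nor are the control odds a plain population average, since the model would condition on baseline PHQ-9 and site.

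It is also fair that the shift is well inside sampling error and touches only secondary outcomes. The rate of a 5-point improvement is unknown and could lie near 50%, where the shift vanishes.

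**Conclusion.** The point holds as a minor one about what is estimated. If the logistic model carries over the intervention-arm-only random coefficient, its odds ratio is not the arm-level comparison the objectives ask for, and equal rates do not give 1 unless the event rate is 50% or navigator variance is zero.

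At the planning ICC on the latent scale the odds ratio under equal rates is about 0.95 at 20% and 0.97 at 30%. It moves to 0.90 and 0.93 at an assumed ICC of 0.10. If the ICC of 0.05 is read on the proportion scale, the values are 0.91 and 0.95. All of these rest on assumed event rates and an assumed binary-scale ICC.

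It would be wrong to conclude that equal rates can never give 1, that the distortion always disfavours the intervention, or that the main result is threatened. The primary outcome is continuous and analysed on the identity scale, so it is unaffected.

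**What to change.** State in the analysis plan that the reported effect for the binary PHQ-9 outcomes is a standardised risk difference and odds ratio. Predicted risks under each allocation are averaged over the observed covariates and, for the intervention arm, over the estimated navigator distribution, with a bootstrap 95% interval. Both measures show no effect when the standardised risks in the two arms are equal. An alternative is to report a risk difference from the same linear mixed model as the primary outcome, where the identity link avoids the problem. The random-effect structure of the logistic model should be written out in either case.

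The cost is some wording and one post-estimation step, with no new data and no change to the primary analysis. The drawback is that the interval depends on a navigator variance estimated from about 12 navigators, so it will be imprecise.
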